### Timeframe of the study

The recruitment of the PCP is planned over 2 months between March and May 2015.

Patients’ eligibility screening and patient inclusion is projected within a period of 4 months. The aim is to include 1 patient/week per PCP.

### Ethics approval

The study protocol is approved by the Ethics Committee of the Canton of Zurich (reference KEK-ZH-number 2015–0595).

### Patient informed consent

Previous to study participation, patients receive written and verbal information about the content and extent of the planned study from the PCPs. In case of acceptance, they sign the informed consent form.

### Data security/disclosure of original documents

The patient names and all other confidential information fall under medical confidentiality rules and are treated according to appropriate Federal Data Security Laws. The patient names are not accessible to the study staff.

### Sample size calculation

Assuming a 0.05 2-sided significance level, 30 clusters (on PCP-level) including 13 patients each would have an 80 % power to detect a difference of 1 drug, which we consider to be clinically relevant.

Based on previous studies [14] we assumed an intracluster correlation coefficient (ICC) of 0.02 for the primary outcome and a standard deviation of 2.8 [21]. In consideration of a drop-out rate of 10 %, 33 PCPs (16 respectively 17 PCPs with 215 patients in each arm) are needed.

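### The stated 80% power does not follow from the stated inputs: 30 clusters of 13 with ICC 0.02 and SD 2.8 give about 86–89%

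*Protocol article*

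**What the plan says.** The section "Sample size calculation" of the protocol article gives all the inputs of a standard two-arm cluster calculation, and its result:

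- Significance level: "Assuming a 0.05 2-sided significance level".
- Size before drop-out: "30 clusters (on PCP-level) including 13 patients each".
- Claimed result: such a trial "would have an 80 % power to detect a difference of 1 drug".
- Correlation and spread: "we assumed an intracluster correlation coefficient (ICC) of 0.02 for the primary outcome and a standard deviation of 2.8". The ICC is referenced to previous studies and the SD to the pilot study.
- After a 10% drop-out allowance, 33 PCPs, given as "16 respectively 17 PCPs with 215 patients in each arm) are needed".

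The 16/17 split of the 33 PCPs shows that 30 is the total number of clusters, so 15 per arm. The paragraph states no allowance for unequal cluster sizes, for a rank test or for any other loss of efficiency.

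**The concern.** A reader who enters these inputs in the usual formula does not get 80%. The gap is too large for rounding or for the choice between normal and t, so the paragraph contradicts itself.

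What is at stake is how much reserve the trial has. If the ICC is 0.02 and the SD 2.8, the design has power close to 90%, and some room for uneven clusters or for clustering by practice. If 80% was obtained with a larger ICC or SD than the text reports, there is no such room. The paragraph justifies the size of the trial for its primary outcome, and as printed a reader cannot tell which case applies.

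**Working it through.** **Inputs**, all from "Sample size calculation": difference d = 1 drug; SD = 2.8; ICC = 0.02; m = 13 patients per cluster; k = 15 clusters per arm, so n = 15 × 13 = 195 patients per arm; two-sided alpha 0.05.

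**The plan's drop-out figures reproduce.** 30 × 1.1 = 33 PCPs, and 195 × 1.1 = 214.5, rounded to 215 patients per arm.

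**The plan's 80% does not reproduce.**

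1. Design effect = 1 + (m − 1) × ICC = 1 + 12 × 0.02 = 1.24.
2. Effective n per arm = 195 / 1.24 = 157.3.
3. Standard error = 2.8 × √(2 / 157.3) = 0.316.
4. d / SE = 1 / 0.3158 = 3.167.
5. Power, normal approximation = Φ(3.167 − 1.960) = Φ(1.207) = 88.6%.
6. Power, noncentral t with 30 − 2 = 28 df = 86.4%. With 388 df (patients minus two) it is 88.5%.

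**Clusters needed for 80% at the stated inputs.** Unclustered n per arm = 2 × 2.8² × (1.960 + 0.842)² / 1² = 123.1. Times 1.24 this is 152.6, and divided by 13 it is 11.7, so 12 clusters per arm. That makes 24 in total, with power 80.9%. On the t distribution it takes 13 per arm, 26 in total (24 df, 80.7%).

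**Detectable difference at 80% power with 30 clusters.** Normal: (1.960 + 0.842) × 0.3158 = 0.88 drug. With t on 28 df: 0.92 drug.

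**Other readings of the text, at ICC 0.02 and SD 2.8:**

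| Reading | Power, normal | Power, t |
|---|---|---|
| 30 clusters of 13, as stated | 88.6% | 86.4% |
| 10% of clusters lost from the 30 (27 left) | 85.2% | 82.3% |
| 10% of patients lost (11.7 per cluster) | 85.9% | 83.4% |
| 33 clusters, 16 and 17 | 91.3% | 89.5% |
| Clustering ignored | 94.1% | 92.6% |
| One-sided 0.05 | 93.6% | not run |
| 30 clusters per arm | 99.4% | not run |

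None comes within 2 points of 80%.

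**What would return 80%, changing one input at a time:**

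- ICC of 0.049 (normal) or 0.040 (t, 28 df). At ICC 0.05 the power is 79.6% or 76.8%.
- SD of 3.17 (normal) or 3.06 (t, 28 df).
- About 10 patients per cluster instead of 13 (81.3% normal, 78.5% t).

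**The case against.** The strongest defence is that this is a condensed article, and that an allowance it does not print may have been built in. Such allowances could close the gap. A cluster-size coefficient of variation of 1.0, which is an assumption, gives a design effect of 1 + (2 × 13 − 1) × 0.02 = 1.5 and a power of 82.1% (normal) or 79.4% (t, 28 df). A worst-case efficiency of 0.864 for a rank test gives 81.1% (t, 28 df). One may also say that 80% was meant as a conventional floor, and that understating power harms nobody.

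Part of this stands. An unprinted allowance cannot be ruled out, and if the ICC and SD are as stated the error is on the safe side. But the text claims 80% outright, not at least 80%. It names no such allowance, and it handles drop-out separately by going from 30 to 33 PCPs. The article prints a full set of inputs and a result, and these disagree whatever a longer document says.

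Three stronger readings are tempting, and the documents do not support them:

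- *That an ICC of 0.04–0.05 must have been used.* It is one candidate among several. A larger SD, smaller clusters or an unstated allowance would also do it, so the text does not show that any particular input was misreported.
- *That the arm sizes are wrong*, because 16 × 13 = 208 and 17 × 13 = 221. The 215 is 195 × 1.1 rounded up, a per-arm target. The totals are 429 and 430.
- *That 34 PCPs are needed*, because 30 / 0.9 = 33.3. Multiplying by 1.1 leaves 429 × 0.9 = 386 patients instead of 390, which is immaterial to the power.

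**Conclusion.** The point holds as a minor internal inconsistency. Under the stated inputs the power is 86.4% to 88.6%, not 80%, an understatement of 6 to 9 percentage points. This rests on equal clusters of 13, 15 per arm, the usual design effect, and an analysis that accounts for clustering.

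The direction is conservative if ICC 0.02 and SD 2.8 are right: the trial then has more power than it claims. It would be unfavourable only if a larger ICC or SD was really assumed. Nothing in the document indicates this, and even at ICC 0.05 the power would be within about 3 points of the claim. The finding shows that the figures disagree. It does not show which one is at fault, or that the trial is too small.

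**What to change.** Keep the planned enrolment and reconcile the paragraph in one of two ways:

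- If ICC 0.02 and SD 2.8 are the planning values, restate the power of 30 clusters of 13 as about 86–89%, and name the method (normal approximation, or t on cluster degrees of freedom).
- If 80% is the result of the calculation actually done, report the ICC, SD or other allowance that produced it, for example one for unequal cluster sizes.

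The cost is the rewording of one paragraph. The number of PCPs, the number of patients and the analysis are unaffected.

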## Discussion

The aim of this study is to determine whether a systematic review with a specific algorithm leads to more appropriate medication use in patients with multimorbidity (60 years and older) without worsening their quality of life and the course of the disease. Up to now, similar interventions have been tested in older populations but not in a primary care setting. In this setting, it is crucial, that an intervention is time-saving for enabling implementation in the daily clinical practice. In the pilot study the expenditure of time was 15 minutes (median; interquartile range (IQR): 10–30). The feasibility and acceptability was rated with a 5-point Likert scale in different items (means: 3.2–4.2, SD 0.83–1.3). Other studies concerning improving appropriate prescription in (mostly older) patients receiving complex polypharmacy present a more time-consuming algorithm or method than usual care [26]. The time aspect might be a strength of our approach in comparison to other ongoing studies [14, 15, 24].

A special feature of our study is the investigation of overtreatment as well as undertreatment. After piloting the study, an extension was made: beside the list of medications in use a special section was added with “medication started.”

Prioritization of patient’s problems is a crucial issue in the shared-decision-making process. To foster this approach and discussions between physician and patient on this issue, we added a list of the four most important complaints from the patient’s perspective to our tool in in parallel with the list of the four major clinical problems defined by the PCP.

Based on other studies [24], measurements of EQ-5D-3 L might even enable an economic evaluation of the danger of adverse drug reactions.

Finally, our study contains an exploratory part, as patient’s barriers and enablers against the approach will be inquired systematically 13 months after intervention. This has the potential to optimize the algorithm or further adapt it to the specific needs of primary care.

### Trial status

Patient recruitment had not started at the first submission in April 2015.

## Abbreviations

GPGP: Good Palliative Geriatric Practice
HbA1c: glycated hemoglobin
ICC: intracluster correlation coefficient
IQR: interquartile range
ITT: intent-to-treat
LOCF: last observation carried forward
PCP: primary care physician
PP: per-protocol
QoL: quality of life
SD: standard deviation
TSH: thyroid-stimulating hormone
